### Outcomes

#### Primary outcome

The primary outcome measure will be self-reported physical function, measured by the PSFS^56 77^ at baseline, 6, 12 and 52 weeks after randomisation. The primary time-point is 6 weeks after randomisation (ie, immediate post-intervention), while the secondary time-points are 12 and 52 weeks after randomisation. The PSFS, originally proposed by Stratford *et al*,^77^ is a valid, reliable and responsive self-report instrument^56^ designed to assess functional change in people with musculoskeletal disorders. Participants identify three important activities they are unable to do or have difficulty with because of their LBP and rate their ability to perform each activity. Each activity is rated on an 11-point numerical rating scale ranging from 0=‘unable to perform activity’ to 10=‘able to perform the activity at preinjury level’. The total score, calculated by summing the numerical ratings for each activity, is provided on a discrete scale ranging from 0 to 30, where higher scores indicate better function.

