### Sample size

The sample size calculation was conducted a priori, considering a MAMS design with five arms (one control arm and four intervention arms) and two stages that consist of one interim and the final analysis. The primary endpoint was established at 6 weeks post-randomisation (ie, immediate post-intervention). A smallest worthwhile effect on the PSFS score (0–30) of 4 points was chosen to estimate the sample size, considering the literature^76^ and the nature of the intervention (ie, a 6-week digital intervention with no face-to-face interaction).

The sample size calculation was based on a two-sided type I error of 5% (significance level), a power of 80% to control for a type II error and an SD of 5.8 using a generalisation of the power requirements for testing multiple active arms to one control group, as proposed by Dunnett.^92^ The calculation resulted in 21 participants per arm at the first stage and 42 participants per arm at the second stage, reaching a total sample size of 315 participants. Allowing for a loss to follow-up rate of 15% at 6 weeks, the study would require a total sample size of 370 participants (n=25 in the first stage and 49 in the second stage per group). This total sample represents the maximum number of participants that will be enrolled when all the intervention arms meet the criteria for being maintained through the second interim stage (ie, no arm is dropped after the interim analysis). Therefore, there is the possibility that the study terminates with a smaller sample size if, at the interim analysis, one or more intervention arms meet the criteria for being dropped. For instance, if one, two or three arms are dropped after the interim, the study sample will decrease to 321, 272 and 223, respectively.

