If the change in an intervention arm is no more than 0.5 points greater than the control group, this intervention arm will be dropped. Under this rule, all four intervention arms may be dropped, and the trial terminated. This decision rule was established based on previous adaptive trials investigating conservative interventions in the field of musculoskeletal health.^96^If the change in one intervention arm is more than 4 points higher than the other, the worst-performing intervention arm will be dropped. This decision rule was established considering the smallest worthwhile effect on disability, reported in previous studies as a 15% incremental improvement beyond the natural recovery.^97^ Natural recovery, in turn, is considered a 30% improvement from baseline. Based on our previous study (EMPoweR), a 45% improvement from baseline would correspond to a 5.4-point between-group difference. For this study, this effect size was downgraded to 4 points due to the nature and duration of the intervention (ie, a 6-week digital intervention with no face-to-face interaction).

The decision rules were carefully designed to minimise the risk of prematurely and incorrectly dropping promising treatment arms, potentially leading to a failure to reject the null hypothesis (type II error), while ensuring that the preplanned adaptations would still guarantee increased trial efficiency. Two complementary decision rules were proposed to account for the comparison between each treatment arm against the control group (first rule) and the pairwise comparison among all treatment arms (second rule). Both decision rules are intended to work as indicators of futility, therefore configuring a ‘drop-the-loser’ design that also allows early stopping for futility. Early stopping for efficacy was not planned in this trial.

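### The 5.4 points called a between-group difference is, on the plan's own definition, total within-arm change; the between-group part is about 1.8 points, so the derivation shown does not support 4

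*Protocol article*

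**What the plan says.** The protocol article uses 4 points on the Patient-Specific Functional Scale (PSFS) total in two places.

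- **Sample size section:** "A smallest worthwhile effect on the PSFS score (0–30) of 4 points was chosen to estimate the sample size". The reasons given are cited literature and the nature of the intervention.
- **Statistical methods, second decision rule:** "If the change in one intervention arm is more than 4 points higher than the other", the worse of the two arms is dropped.

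Only the second place shows a derivation, in four steps:

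1. The smallest worthwhile effect on disability is "reported in previous studies as a 15% incremental improvement beyond the natural recovery".
2. "Natural recovery, in turn, is considered a 30% improvement from baseline".
3. On the basis of the sponsor's earlier eHealth physiotherapy trial, "a 45% improvement from baseline would correspond to a 5.4-point between-group difference".
4. "this effect size was downgraded to 4 points due to the nature and duration of the intervention".

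The Primary outcome section says that the PSFS total "is provided on a discrete scale ranging from 0 to 30".

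**The concern.** Steps 1 and 2 add up to the 45% in step 3, so 45% is the whole improvement from baseline expected in an arm that recovers naturally and also gains the worthwhile increment. A concurrent control arm recovers naturally too. The difference between the arms is then the increment alone, but step 3 attaches the between-group label to the total.

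Two uses of the 4 points inherit the problem. The sample size calls 4 the smallest worthwhile effect and gives the same delivery-mode reason as step 4. Rule 2 compares two active arms, both of which recover naturally, so a threshold built from a total that includes recovery has no evident meaning there.

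What is at stake is how the trial describes what it can detect and how its results are later read. A reader who takes 4 as the least benefit worth having will think the trial well powered for that quantity. The plan's own definition points to a much smaller one.

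**Working it through.** **Inputs.** From Statistical methods: increment 15%, natural recovery 30%, and 45% equated with 5.4 points. From Primary outcome: scale 0 to 30. From Sample size: effect 4 points, SD 5.8, two-sided 5%, 80% power, Dunnett comparison of four active arms with one control, and 21 + 42 = 63 evaluable per arm. The baseline mean of the earlier trial is not given.

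**Step 1: the plan's 5.4.** If 45% of baseline is 5.4, the implied baseline is 5.4/0.45 = 12. It splits as follows:

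- natural recovery: 0.30 × 12 = 3.6 points
- increment beyond it: 0.15 × 12 = 1.8 points
- total: 3.6 + 1.8 = 5.4 points

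The increment needs only the ratio: 5.4 × 15/45 = 1.8.

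**Step 2: can the label be rescued?**

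- If 5.4 were the 15% increment, baseline would be 5.4/0.15 = 36, above the scale maximum of 30.
- If 4 were the 15% increment, baseline would be 4/0.15 = 26.7. That contradicts 45% = 5.4, and 30% recovery alone would take the score to 26.7 × 1.30 = 34.7, again off the scale.
- Against a baseline of 12, 4 points is 4/12 = 33%, and 4/1.8 = 2.2 times the increment.

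**Step 3: range.** If the earlier trial's baseline is instead assumed to lie between 9 and 15, 15% of it is 1.35 to 2.25 points, still well below 4.

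**Step 4: power with the stated numbers.** SE = 5.8 × √(2/63) = 1.033. Power = Φ(δ/SE − c), with c = 2.442 (two-sided Dunnett, four comparisons) or c = 1.96 (unadjusted).

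| True difference | Dunnett | Unadjusted |
|---|---|---|
| 1.8 | Φ(1.742 − 2.442) = 24% | Φ(1.742 − 1.96) = 41% |
| 3 | Φ(2.903 − 2.442) = 68% | Φ(2.903 − 1.96) = 83% |
| 4 | Φ(3.871 − 2.442) = 92% | Φ(3.871 − 1.96) = 97% |

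Simulating both dropping rules, with the other three arms null, moves the 1.8-point figures only to 23% and 38%.

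These figures take 63 per arm as given. The single-stage Dunnett formula at 4 points gives 2 × [5.8 × (2.442 + 0.842)/4]² = 45.4, so 46 per arm. The stated 63 is not reproduced, but that is a separate matter and the 1.8 does not depend on it.

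**Step 5: reading a final interval.** An unadjusted 95% interval has half-width 1.96 × 1.033 = 2.0. For illustration, an estimate of 1.0 gives −1.0 to 3.0, which excludes 4 but contains 1.8.

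**Step 6: rule 2.** At 21 per arm, SE = 5.8 × √(2/21) = 1.79, taking 5.8 as the SD of change. For two equally good arms, a gap above 4 in either direction has probability 2 × [1 − Φ(4/1.79)] ≈ 2.5%. A gap above 1.8 has probability about 31%.

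**The case against.** Several objections limit the point, and most of them stand.

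- **Four points may have independent support.** The Sample size section cites a different source from the one behind rule 2, and that source is not shown. The derivation fails, but it does not follow that 4 is wrong.
- **1.8 is not an established value for this outcome.** The 15% figure concerns disability, which the trial measures with a separate questionnaire. The baseline of 12 is back-calculated, and the slip could lie in the wording of the 45% sentence. So 1.8 is what the plan's own definition implies and no more. A reader might infer that the trial should be resized, to about 224 per arm: 2 × [5.8 × (2.442 + 0.842)/1.8]² = 223.9. The documents do not support that.
- **Effects between 1.8 and 4 would not all be missed.** A reader might infer this, but power at 3 points is 68% to 83%. The weakness lies at the lower end.
- **Nothing says that results will be judged against 4.** The article states only p < 0.05 as its criterion. It also collects each participant's own smallest worthwhile PSFS score at baseline. That measure asks for a score to be achieved, so it does not directly give an increment over control and does not repair the derivation.
- **Rule 1 is unaffected.** Its 0.5-point threshold has its own source, so any risk of dropping a useful arm under it is not a consequence of this error.
- **Rule 2 is not shown to do harm.** A higher threshold drops fewer arms, which fits the stated aim of protecting promising ones.

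What remains untouched is that the between-group label is wrong as written and the step from 5.4 to 4 inherits it.

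**Conclusion.** The point holds as a mislabelled figure and an unsupported derivation. Under the plan's definition, 5.4 points is total within-arm change and the between-group part is 1.8 points (1.35 to 2.25 for an assumed baseline of 9 to 15). The only derivation shown therefore supports 4 neither as the smallest worthwhile effect nor as a threshold between two active arms. This rests on reading 45% as 30% + 15% of one baseline, which the text invites and which the 0 to 30 scale all but forces.

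In size, 4 is about 2.2 times the implied increment. Power at 1.8 is about 24% (Dunnett) or 41% (unadjusted), given 63 evaluable per arm and SD 5.8. The rationale should be corrected before results are interpreted, but no redesign follows from it.

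**What to change.** 1. In Statistical methods, relabel 5.4 points as within-group change and state that the cited definition implies about 1.8 points between groups.
2. In Sample size, call 4 points the target difference, unless the literature cited there supports it as the smallest worthwhile effect on the PSFS. If it does, say so.
3. Disclose power at about 1.8 points beside the power at 4.
4. State that a final confidence interval containing 1.8 will not be read as excluding a worthwhile effect.
5. Justify the rule 2 threshold as a gap between two active arms, without reference to natural recovery. Its value need not change.

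The cost is wording in the protocol and analysis plan and a less favourable power statement at the smaller effect. Enrolment, tests and thresholds stay as they are.

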### Data monitoring committee

An independent DSMB will be established as an oversight role to monitor the overall conduct of the trial, regularly review accumulating trial data and ensure compliance with scientific, regulatory and ethical standards. The DSMB will be a multidisciplinary group composed of academics/clinicians convened yearly. During the development stage, the DSMB will ensure data integrity. When identified, omissions, inconsistencies or errors will be explored and resolved. Based on the results of the interim analyses and in accordance with the prespecified decision rules, the DSMB will make recommendations to the Internal Trial Committee (ITC) regarding the progress and conduct of the trial (ie, advising the ITC on whether each intervention arm should be maintained or dropped across interim stages, or even whether the trial should be terminated for futility). For this reason, the board members will not be blinded to allocation to enable a more comprehensive and integrated data review.

### Trial monitoring

An ITC will be established to monitor all aspects of the conduct and progress of the clinical trial, ensuring adherence to the protocol, monitoring adverse events and safeguarding participants’ safety and the trial’s quality. The ITC will be composed of the principal investigator, the trial coordinator and at least another co-investigator, convening weekly. The principal investigator will be responsible for overseeing participants’ safety and safeguarding their best interests. The principal investigator will be blinded to allocation, unless unblinding is essential to ensure the participant’s safety.

## Ethics and dissemination

### Research ethics approval

This study has been prospectively approved by the HREC of The University of Sydney (HREC Approval No. 2023/HE000772) and prospectively registered with the Australian New Zealand Clinical Trials Registry (ANZCTR) (https://www.anzctr.org.au/) (Trial Registration: ACTRN12624000319572; Registration date: 25 March 2024). A Universal Trial Number (UTN) has been generated (U1111-1301-6286). Informed consent will be obtained from all participants.

### Dissemination policy

The findings of this study will be disseminated to the scientific community through publications in relevant peer-reviewed journals, reports and presentations at scientific forums and conferences. Participants will be provided with a summary of the study findings in lay language. The study results will also be strategically disseminated to the wider community and relevant policymakers to increase awareness of evidence-based recommendations. We will seek to establish a partnership with Musculoskeletal Health Australia to share the study findings with their network of researchers and consumers, boosting the breadth and depth of our communication capabilities.

### Protocol amendments

This protocol is version number 6, dated 12 December 2024. Any changes to the study protocol will be submitted to the HREC for review and approval and acknowledged by the study sponsor prior to implementation.

### Consent or assent

Informed consent will be obtained from all participants before any study-related procedures. After reading the Participant Information Statement (online supplemental material 1), potentially eligible participants who are willing to participate in the trial and comply with the study procedures will be invited to the consent procedures via REDCap. The online signature will be collected by ticking a box and selecting ‘proceed’ on the online Participant Consent Form (online supplemental material 2).

### Confidentiality

Access to the data collected during the trial will be restricted to the principal investigator, the trial coordinator and members of the research team, according to prespecified blinding arrangements. Participants’ privacy will be protected, and data confidentiality will be maintained during all the stages of the study, for archiving and storage, and for publication and dissemination purposes. Study data and associated records will be exported and stored in a re-identifiable (coded) format on a password-protected research data storage infrastructure hosted and managed by the University of Sydney. Once data collection is completed, identifiers will be removed from the dataset to protect participants’ privacy.

### Ancillary and post-trial care

All participants will have access to specific components of the app (according to their group allocation) during the entire study (ie, 1 year after the last recruited participant completes the intervention period). After this period, we will offer offline access to the full content of the app to all participants in the study for an additional 6 weeks.

### Trial registration

This trial has been prospectively registered with the Australian New Zealand Clinical Trials Registry (ANZCTR) (http://www.anzctr.org.au/) (ACTRN12624000319572; Registration Date: 25 March 2024) prior to the enrolment of the first participant. A Universal Trial Number (UTN) has been generated (U1111-1301-6286).

### Protocol and statistical analysis plan

The full statistical analysis plan will not be published alongside this study protocol.

### Data sharing

The datasets generated and/or analysed during the current study will be available from the corresponding author on reasonable request. The datasets will not be made publicly available due to restrictions in participants’ consent regarding their data being shared by the University of Sydney.
